## Abstract

**Background:**

This is a protocol for a prospective longitudinal study that aims to investigate: (1) group-by-time changes over a minimum of 15 months follow-up in patellofemoral pain (PFP) symptoms, biomechanical, muscle function, pain processing, and psychological features; (2) the extent to which changes in biomechanical, muscle function, pain processing, and psychological features are associated with changes in self-reported pain, physical performance measures, self-reported function, health-related quality of life (HRQOL), and physical activity level.

**Methods:**

Individuals with PFP (*n* = 144) and control individuals (*n* = 85) without PFP were assessed at baseline. Outcomes assessed included: 3D kinematics and kinetics during single leg squat, step-down and single leg hop; maximal torque and rate of torque development of hip abductors and knee extensors/flexors; force steadiness of hip abductors and knee extensors; anterior and lateral trunk endurance; pressure pain thresholds at the center of patella and contralateral shoulder; kinesiophobia (Tampa Scale for Kinesiophobia); pain catastrophizing (Pain Catastrophizing Scale); worst self-reported pain (Visual Analogue Scale); physical performance measures (Single Leg Hop Test and Forward Step-Down Test); self-reported function (Anterior Knee Pain Scale); HRQOL (Medical Outcome Short-Form 36), and physical activity level (Baecke’s Questionnaire). Follow-up assessments will be identical to the baseline and will be performed after a minimum of 15 months. Generalized linear mixed model (GLMM) will be used to investigate group-by-time differences. Linear regression models will be used to determine the extent to which changes in biomechanical, muscle function, pain processing, and psychological features are associated with changes in self-reported pain, physical performance measures, self-reported function, HRQOL, and physical activity level.

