### Procedures

2.2.

Follow-up assessments will be performed in two separate days, identically to the baseline (Figure 1). In the first day, characteristics of the participants, self-reported measures, Pressure Pain Thresholds (PPTs), physical performance measures, anterior and lateral trunk endurance, 3D kinematics and kinetics will be assessed. Participants will be oriented to perform all tasks barefoot and wear light clothes. In the second day, maximal torque, rate of torque development (RTD), and force steadiness of the hip abductors and knee extensors/flexors will be assessed. Physical performance measures and lateral trunk endurance will be assessed bilaterally, while PPTs, 3D kinematics and kinetics, and muscle function measures will be assessed in the symptomatic or most symptomatic knee (bilateral symptoms) in individuals with PFP. For controls, the assessed limb will be randomly selected. The same limb assessed in the baseline will be collected in the follow-up. At least 15 months after the baseline assessment, participants will be contacted by phone or e-mail and invited to return to the follow-up assessment.

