### Statistical analysis

2.10.

Descriptive statistics (mean, median, standard deviation, and interquartile intervals) will be calculated for all variables of interest. Generalized Linear Mixed Model (GLMM) will be used to investigate group-by-time differences. The type of matrix will be chosen according to the Akaike Information Criterion (AIC) in order to assess the adherence index of the model (56). The lower the AIC, the higher the adherence (56). Group and time interaction effects will be considered fixed, while participant effects will be considered random. Pairwise comparisons will be performed with Bonferroni *post hoc* tests when significant interactions or main effects are determined. Mean differences [95% confidence intervals (CI)] and effect sizes (Cohen’s *d* [95% CI]) for each *post hoc* comparison will be calculated. The guidelines for interpreting the Cohen’s *d* are: 0 to 0.40 small effect, 0.41 to 0.70 moderate effect, 0.71 or large effect (57). Statistical significance level will be set at .05.

For the first stage of the regression analyses, univariate linear regression models will be used to determine to what extent changes in each biomechanical, muscle function, pain processing and psychological features are associated with changes in self-reported pain, physical performance measures, self-reported function, HRQOL and physical activity level in individuals with PFP. A significance level of *p* ≤ .10 rather than the conventional level of *p* < .05 will be used to ensure that the univariate analyses are sufficiently sensitive to identify potential prognostic factors for entry in the model (58). For the second stage, all potential prognostic factors that showed significant associations on univariate analyses will be entered into a stepwise multivariate linear regression with backward elimination (*p* ≤ .10) in order to identify a group of factors that are independently associated with the clinical outcomes. For the final multivariate models, the significance will be set at .01 to minimize the results being adversely influenced by the likelihood of increased risk of Type I error associated with multiple analyses. The predictive power of each final model will be determined by calculation of the percentage of explained variance (adjusted *R*^2^).

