The investigation of the natural course of PFP can provide additional insights. For instance, PFJ stress has been suggested to play a central role in PFP pathophysiology (9). However, its behavior over time in individuals with PFP has never been investigated. As physical and non-physical features are thought to contribute to PFJ stress (9, 63–65), our study will be able to provide data regarding which features have associations with changes in PFJ stress in the long-term.

This study has some limitations that should be acknowledged. Only young adults were included in our study, limiting the generalizability of our findings to adolescents and older individuals. Our study will provide insights regarding the natural history of physical and non-physical features in individuals with PFP, however, cause and effect cannot be established given the study design. Lastly, this prospective study includes assessments in only two time points (i.e., baseline and follow-up). As PFP is characterized by intermittent symptoms (1), this may have an influence on the results.

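### Follow-up has a 15-month floor but no upper limit, and the described models carry no elapsed-time term, so unequal intervals could bias the group-by-time contrast

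*Protocol article*

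**What the plan says.** The abstract states the timing of the second visit as "Follow-up assessments will be identical to the baseline and will be performed after a minimum of 15 months". Section 2.2 (Procedures) describes how it comes about: "At least 15 months after the baseline assessment, participants will be contacted by phone or e-mail and invited to return to the follow-up assessment". The Introduction and Discussion repeat the lower bound. No upper limit, target date or visit window appears, and nothing matches the timing of the two groups.

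The Discussion confirms that "this prospective study includes assessments in only two time points (i.e., baseline and follow-up". In section 2.10 (Statistical analysis) the mixed model is described as follows: "Group and time interaction effects will be considered fixed, while participant effects will be considered random". It continues with "Pairwise comparisons will be performed with Bonferroni *post hoc* tests when significant interactions or main effects are determined". Two visits followed by pairwise comparisons imply that time enters as a two-level factor, although the article does not use those words.

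For the second aim, section 2.10 says that "univariate linear regression models will be used to determine to what extent changes in each biomechanical, muscle function" and the other features are associated with changes in the clinical outcomes, within the PFP group. Then "all potential prognostic factors that showed significant associations on univariate analyses will be entered into a stepwise multivariate linear regression" with backward elimination. The candidates are the features themselves. No covariate is forced in, and elapsed time is not mentioned.

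**The concern.** The study is about change over time. The Introduction expects people with PFP to worsen, their differences from controls to widen, and changes in features to follow changes in outcomes. If that is so, a return at 15 months and a return much later are different exposures, yet both are coded as the same follow-up level.

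Three things could follow:

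- If the groups' mean intervals differ and outcomes drift in both groups, the interaction picks up drift multiplied by the gap in intervals, even when the two groups change at the same rate.
- If the intervals are matched, there is no such artefact. The estimate is still an average over whatever intervals occurred, so the result cannot be attached to a stated length of follow-up.
- Within the PFP group, interval length could act as a shared cause of feature change and outcome change.

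The limitations paragraph mentions the two time points and intermittent symptoms, but not unequal follow-up.

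**Working it through.** The article gives no error-rate or power figure that bears on this point, so there is nothing of its own to reproduce. The calculations below are illustrations.

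**Inputs from the article.** Baseline sizes are 144 and 85 ("Individuals with PFP (*n* = 144) and control individuals (*n* = 85) without PFP were assessed at baseline"). Section 2.10 gives a significance level of .05 for the mixed model (two-sided assumed), .10 for univariate screening and .01 for the final regression models.

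**Assumed inputs.** These are the monthly drift, the gap in mean interval between groups, and the spread of intervals. Change scores are scaled to SD 1.

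**Group-by-time contrast.** Suppose both groups drift at the same monthly rate, so there is no true difference in rate.

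- Standard error: √(1/144 + 1/85) = √(0.00694 + 0.01176) = 0.137 SD.
- False interaction: δ = gap × monthly drift.
- Rejection rate: Φ(δ/SE − 1.96) + Φ(−δ/SE − 1.96).

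| Gap in mean interval | Drift per month | δ (SD) | Type I error |
|---|---|---|---|
| 0 months | any | 0 | 0.05 |
| 3 months | 0.01 | 0.03 | 0.06 |
| 3 months | 0.03 | 0.09 | 0.10 |
| 6 months | 0.01 | 0.06 | 0.07 |
| 6 months | 0.02 | 0.12 | 0.14 |
| 6 months | 0.03 | 0.18 | 0.26 |

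The assumed drift equals 0.15 to 0.45 SD over 15 months (15 × 0.01 and 15 × 0.03).

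**Effect of attrition.** With an assumed 30% loss in each group, SE = 0.137/√0.7 = 0.164. The largest case becomes 0.18/0.164 = 1.10, and the type I error falls from 0.26 to about 0.20.

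**Change-on-change regressions.** Let feature change and outcome change each drift by b per month and otherwise be independent, with n = 144 and intervals uniform from 15 to U months. Then Var(T) = (U − 15)²/12, and the induced correlation is r = b²Var(T)/(b²Var(T) + 1). Two worked cases:

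- U = 24, drift 0.5 SD per 15 months: Var(T) = 81/12 = 6.75, b² = (0.5/15)² = 0.00111, r = 0.0075/1.0075 = 0.007.
- U = 36, drift 1.0 SD per 15 months: Var(T) = 441/12 = 36.75, b² = (1/15)² = 0.00444, r = 0.163/1.163 = 0.140.

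False screening rates at p ≤ .10, from 10,000 simulated data sets per scenario:

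| Intervals | Drift 0.2 SD per 15 months | 0.5 SD | 1.0 SD |
|---|---|---|---|
| 15-18 months | 0.11 | 0.10 | 0.10 |
| 15-24 months | 0.10 | 0.10 | 0.13 |
| 15-36 months | 0.10 | 0.13 | 0.51 |

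The 0.11 is 0.105 rounded, which is nominal within simulation error. With elapsed time as a covariate, the rate was 0.096 to 0.105 in every scenario. The later .01 criterion was not simulated.

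**The case against.** A reader might infer that unequal follow-up will be mistaken for group or feature effects. The article does not support that. Section 2.2 describes one contact procedure for everyone, and nothing suggests that the groups are invited at different times. No actual intervals are reported, and no drift is documented.

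The common-drift assumption also matters. The controls have a mean age of 22 and are excluded at follow-up if they develop knee pain, so on many measures they may hardly drift. If neither group drifts, a gap in intervals creates nothing. If only the PFP group drifts, the interaction is real, and interval length alters its size without creating a false positive. The 0.26 figure combines the larger gap with the steepest assumed drift, and it uses baseline numbers although section 2.1 applies further exclusions at follow-up.

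The regression part is weaker still. For 15-24 months the screening rate stays near nominal unless drift is very strong, and the final models are judged at .01.

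Finally, a condensed article may leave covariates to a fuller analysis plan that is not shown.

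All of this limits the size and certainty of the problem, and it stands. It does not remove the point. The open-ended interval is a design rule fixed in the visible text. The article also spells out the fixed and random effects and the rule for entering regression terms, and that rule leaves no place for elapsed time. With no upper limit, nothing stated keeps the spread small or the groups aligned.

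**Conclusion.** The point holds as a conditional risk. The interval has a floor and no upper limit, and the described models do not account for it.

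Bias in the group-by-time contrast requires both a between-group difference in interval and drift that controls share. Under those assumptions and baseline sample sizes, type I error is about 0.06-0.10 for a 3-month gap and 0.07-0.26 for a 6-month gap, less after attrition. These figures show scale only and do not predict what this study will find.

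The undefined average follow-up is a problem of interpretation that needs no between-group gap, only intervals that vary and change that continues beyond 15 months. Confounding of the change regressions is minor, and material only with a wide spread of intervals and strong drift.

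The change is worth making because it is cheap and section 2 says follow-up is still under way.

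**What to change.** - **Mixed model.** Keep the two-level time factor. Add months from baseline to follow-up, centred at a stated common value, as a term acting at the second visit. With a common drift, the interaction then compares the groups at the same interval. Replacing time by continuous months is less suitable, because it imposes linear change on two points per person in a condition that the article describes as intermittent.
- **Change regressions.** Force the same covariate into every univariate and multivariate model, exempt from screening and elimination.
- **Reporting.** Give the distribution of the interval by group.
- **Conduct.** While follow-up is running, set a latest return date and invite both groups in parallel. The covariate cannot fully replace this: the less the two groups' intervals overlap, the less the data can separate group from elapsed time.

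The cost is one extra covariate per model and one scheduling instruction. The covariate comes from visit dates, which the article does not say are kept but which should be available. A few late returners may fall outside the window.

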**Discussion:**

Physical and non-physical features have been previously associated with PFP. However, the present study will be the first to investigate their integrated evolution as part of the natural history of PFP and its progression. In doing so, we will be able to determine their behavior in the long-term, as well as how they prospectively associate with each other and with clinical outcomes. Ultimately, this will provide a greater understanding of predictors of long-term outcome and possible targets for interventions.

## Introduction

1.

Patellofemoral pain (PFP) is characterized by an insidious onset of pain at the anterior/peri/retropatellar region of the knee (1). Its prevalence is approximately 25% in the general population and 35% in professional athletes (2). Disability, reduced physical activity, and impaired social life are reported in those with PFP (3, 4). Other impairments such as lower self-reported function, physical performance, and health-related quality of life (HRQOL) have also been reported in individuals with PFP, alongside with a possible progression to osteoarthritis (5–8).

PFP is multifactorial and involves a number of physical (e.g., kinetics, kinematics, muscle function) and non-physical features (e.g., psychological or lifestyle factors) (9–11). Proximal, local, and distal kinematics, kinetics, and muscle function impairments have been reported in those with PFP (1, 9, 12–17), and linked with increases in patellofemoral joint (PFJ) load during various tasks (9), a factor suggested to play a central role in PFP (9). Beyond this pathomechanical model of PFP (8), there is an increased awareness that non-physical features may be important in understanding PFP (18). Pain processing (e.g., local and central sensitization) and psychological features (e.g., kinesiophobia and pain catastrophizing) have also been reported to be altered in individuals with PFP (10, 11). Both physical and non-physical features are associated with worse pain, function, and disability (19–22). Some associations among physical and non-physical features with PFP are still not clear, including their prospective association in the long-term. The prospective association of PFJ load with PFP has also not been investigated, despite its proposed critical role (9).

PFP is not self-limiting and is challenging to manage, with symptoms persisting for nearly two decades. Long-term pain is reported to continue in one of every two patients even after treatment (3, 23). Symptom severity may remain unchanged or increase in 50% of affected individuals (24, 25). As such, a similar prospective pattern would also be expected for physical and non-physical features given their previously reported cross-sectional association with PFP. Symptoms duration of individuals with PFP has been previously associated with biomechanical (26) and muscle function parameters (27), as well as pain itself (27, 28). However, the majority of the studies conducted to date have a cross-sectional or interventional design, which precludes the understanding of the natural history of these features in individuals with PFP.

Understanding changes over time in physical and non-physical features in individuals with PFP is a first step to gain knowledge regarding their evolution as part of PFP and its progression. In addition, investigating the prospective association of clinical outcomes (i.e., self-reported pain, physical performance measures, self-reported function, HRQOL and physical activity level) with physical and non-physical features may contribute to the identification of predictors of pain and disability in the long-term, as well as possible targets for interventions.

We have, therefore, designed a prospective longitudinal study aiming to investigate group-by-time changes over a minimum of 15 months in individuals with PFP, measuring their biomechanical, muscle function, pain processing, psychological features and clinical outcomes. In addition, we aim to investigate the extent to which changes in biomechanical, muscle function, pain processing, and psychological features are associated with changes in clinical outcomes. We hypothesize that: (1) individuals with PFP will present worse biomechanical, muscle function, pain processing, psychological features, and clinical outcomes at follow-up as compared to baseline; (2) potential differences in outcomes as compared to asymptomatic individuals at baseline will increase at follow-up; (3) changes over the time in biomechanical, muscle function, pain processing, and psychological features will be associated with changes in clinical outcomes; (4) there will be an association between changes over the time in biomechanical and psychological features.

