### Participants

2.1.

Participants aged 18 to 40 years were recruited through advertisements at social media, universities, gyms and public parks and divided in two groups: individuals with PFP (*n* = 144) and control individuals without PFP (*n* = 85). The following inclusion criteria were considered for PFP group (29): (i) Insidious symptoms of PFP lasting at least three months, (ii) worst knee pain in the last month of at least 20 mm on a 0–100 mm Visual Analogue Pain Scale (VAS), (iii) symptoms of PFP during activities that load patellofemoral joint (e.g., squatting, running, jumping, prolonged sitting, stair negotiation). To be included in the control group, participants had no signs or symptoms of PFP or other neurological or lower limb musculoskeletal conditions. Exclusion criteria for both groups were history of: patellar subluxation, surgery in any lower limb joint, trauma or injury at the knee, or ligament instability. Additional exclusion criteria for the follow-up assessments are: (i) occurrence of knee trauma or injury (both groups); (ii) development of knee pain (only for control group); (iii) development of other medical conditions that may influence the findings (both groups). Participants’ baseline demographics are presented in Table 1.

**Table 1 T1:** Participants’ demographics at baseline.

Variables	PFP group (*n* = 144) Mean ± SD	Control group (*n* = 85) Mean ± SD
Females (*n*)	108	64
Males (*n*)	36	21
Age (years)	23 ± 5	22 ± 3
Height (cm)	166 ± 8	165 ± 9
Body mass (kg)	68 ± 14	62 ± 13
BMI (kg/cm^2^)	25 ± 4	23 ± 4

Abbreviations: SD, standard deviation; PFP, patellofemoral pain; BMI, body mass index.

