### Characteristics of the participants and self-reported measures

2.3.

Age, pain laterality, and duration of PFP symptoms in months will be initially obtained. Weight and height will be assessed using a calibrated scale with a stadiometer (WELMY 110; WELMY, Brazil). Knee and ankle width will be measured using a pachymeter (150 mm × 0.05 mm/6”X1/128”; MARBERG, China) and lower limb length will be measured with a measuring tape from the anterior superior iliac spine to the medial malleolus. The anthropometric measures will be posteriorly included in the biomechanical model. Percentages of body fat and skeletal muscle mass will be assessed using a bioelectrical impedance analyzer (OMRON HBF 514C; OMRON Healthcare; Japan) and calculated with valid and reliable equations provided by the manufacturer (30). Subscapular, triceps, biceps and suprailiac skinfolds will be measured with a caliper (CESCORF TOP TEC; CESCORF, Brazil) following the recommendations of the International Standards for Anthropometric Assessment (31). The measures will be obtained along the right side of the body for 3 consecutive times, and the mean will be used for statistical analysis. Afterwards, participants will answer self-administered scales and questionnaires translated and cross-culturally adapted for the Brazilian population, which are detailed below (32–36).

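### The PFP change regressions give baseline symptom duration no role, although the article links duration to features and to pain; if duration also predicts change, part of the reported associations would be spurious

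*Protocol article*

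**What the plan says.** All references are to the protocol article.

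- **Entry (section 2.1).** The PFP group needs "Insidious symptoms of PFP lasting at least three months". No upper limit is given. The age range is 18 to 40 years. Table 1 gives a mean age of 23 (SD 5) in the PFP group and no row for symptom duration.
- **Background (Introduction).** The article describes PFP as not self-limiting, "with symptoms persisting for nearly two decades". On duration itself it states: "Symptoms duration of individuals with PFP has been previously associated with biomechanical (26) and muscle function parameters (27), as well as pain itself (27, 28".
- **Data collected (section 2.3).** "Age, pain laterality, and duration of PFP symptoms in months will be initially obtained". Section 2.2 says follow-up is performed in the same way as baseline, so a baseline value can be taken to exist.
- **Mixed model (section 2.10).** "Group and time interaction effects will be considered fixed, while participant effects will be considered random". No covariate is named.
- **Regressions (section 2.10).** Stage one asks to what extent "changes in each biomechanical, muscle function, pain processing and psychological features are associated with changes in self-reported pain" and the other clinical outcomes, within the PFP group. In stage two, "all potential prognostic factors that showed significant associations on univariate analyses will be entered into a stepwise multivariate linear regression with backward elimination". The purpose is to find factors with independent associations, and the final models are judged at .01.
- **Limitations (Discussion).** These cover the age range, causality and the two time points. Mixed symptom duration is not among them.

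**The concern.** Section 2.10 does more than stay silent on covariates. It fixes a candidate set (changes in four feature families) and an entry rule (the p ≤ .10 screen, then backward elimination). Duration is not a candidate, and nothing is forced into the model. Yet the procedure is meant to identify factors independently associated with outcome, and the article puts them forward as predictors of long-term outcome and possible intervention targets.

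If people early in the course of PFP and people with long-standing PFP change at different rates, in both a feature and an outcome, the two changes will correlate through stage of disease alone. The screen cannot tell such a feature from one with a link of its own.

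A separate question of interpretation affects the PFP course. With open-ended entry, the mean PFP change is an average over whatever mix of early and long-standing cases was recruited. Described simply as natural history, it hides that mix.

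**Working it through.** The article gives no figure on this point to reproduce: it reports no duration data and no correlation of duration with anything. The calculation below illustrates size under stated assumptions.

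**Inputs from the document:** PFP group n = 144 (section 2.1); screening level .10, two-sided, and final-model level .01 (section 2.10).

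**Assumptions:** duration correlates r₁ with the change in a feature and r₂ with the change in an outcome, linearly; the two changes have no other link; r₁ = r₂, from 0 to 0.4. A return of 115 is an assumed retention figure.

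**Step 1, induced correlation.** With duration as the only common cause, r = r₁ × r₂. For example, 0.3 × 0.3 = 0.09 and 0.4 × 0.4 = 0.16. If either link is zero, r = 0.

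**Step 2, what the screen requires.** Critical |r| = t / √(n − 2 + t²), with t the 95th percentile on n − 2 degrees of freedom. This gives about 0.138 at n = 144 and 0.154 at n = 115.

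**Step 3, chance of passing (Fisher z).** With m = atanh(r) × √(n − 3), P = Φ(m − z) + Φ(−m − z), where z = 1.645 for the .10 level. Worked case, r = 0.16 and n = 144: atanh(0.16) = 0.1614, √141 = 11.874, m = 1.916, so P = Φ(0.272) + Φ(−3.56) ≈ 0.607.

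| Assumed correlation of duration with both changes | Induced r | Passes p ≤ .10, n = 144 | Passes p ≤ .10, n = 115 | Single-predictor p ≤ .01, n = 144 |
|---|---|---|---|---|
| 0 | 0 | 10% | 10% | 1.0% |
| 0.1 | 0.01 | 10% | 10% | 1.1% |
| 0.2 | 0.04 | 14% | 13% | 1.9% |
| 0.3 | 0.09 | 29% | 25% | 6.6% |
| 0.4 | 0.16 | 61% | 53% | 26% |

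The last column is a one-predictor test, not the full stepwise procedure. It shows that the stricter .01 level reduces the excess but does not remove it.

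**Step 4, levels versus change.** A simulation of 4,000 runs at n = 144 separated the two kinds of link. With duration correlated 0.5 with baseline levels and 0 with changes, the mean induced r was 0.00 and about 9% passed the screen. With a correlation of 0.3 with changes, the mean r was 0.09 and 29% to 31% passed, whether or not levels were also linked. The first result follows by construction, because a stable level cancels from a difference. Only a link with change matters.

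**Step 5, effect of adjustment.** With duration in the model and a linear link, the numerator of the partial correlation is r − r₁r₂ = 0, so the induced part disappears.

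**The case against.** The strongest reply is that the Introduction never says duration predicts change. It reports past associations with biomechanics, muscle function and pain, and then notes that most existing studies are cross-sectional or interventional. The planned regressions relate change to change, so stable differences tied to duration drop out. This stands: a reader might infer that duration is, on the article's own word, a confounder of the change models, and the document does not support that. The concern still remains plausible. If levels differ by duration because features evolve over the course of PFP, and that evolution is not linear, the rate of change depends on duration.

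Four further points carry weight.

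- A reader might also infer that duration confounds the natural-history or group-by-time estimate. It does not. Controls have no symptom duration to adjust for, and a mean change is not confounded by the duration of the people averaged.
- A reader might infer that the cohort does mix recent PFP with PFP of many years, or is dominated by long-standing cases. The criteria allow this, but no duration distribution is given. The reference to two decades is background, and a mean age of 23 limits very long durations for most participants.
- The Introduction's statement covers two of four feature families and one of five outcome domains. Using the same covariate in all PFP change regressions is therefore a choice made for consistency and not something the article establishes.
- The aim is associational, and the article disclaims cause and effect. Its mention of intervention targets nevertheless invites a stronger reading of the results.

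A fuller plan, not shown, might add covariates. That softens the point but does not remove it, because the stated candidate set and entry rule leave duration no place.

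**Conclusion.** The point holds as a conditional one. Open-ended entry, a recorded duration variable, the article's own statement that duration is relevant, and regressions that exclude it are all in the text. Whether the exclusion biases anything depends on a link between duration and change that the documents neither show nor rule out.

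The size runs from nil to serious. At n = 144 the chance that a feature with no direct link passes the .10 screen goes from the nominal 10%, when duration is unrelated to change, to about 61% at assumed correlations of 0.4 with both changes. The documents do not allow the study to be placed within that range. The figures assume linear links of equal size and no other connection between the two changes.

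For the group-by-time and PFP-change estimates, the conclusion is limited to heterogeneity: the average is hard to interpret while the mix of disease stages is unreported. The change is worth making because it is cheap and the variable already exists, not because bias has been demonstrated.

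**What to change.** In section 2.10:

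1. Include baseline symptom duration, for example as log months, as a prespecified covariate in the PFP change regressions, both the single-feature models and the multivariable ones. Keep it in whatever its p-value, outside the screen and the backward elimination.
2. Within the PFP group, examine a duration-by-time term and report the estimated change at durations that the observed data support.
3. Report the distribution of baseline duration with the other baseline characteristics in Table 1.
4. State, there and in the limitations, that the natural-history result applies to prevalent PFP of at least three months' duration and averages over the mix of durations recruited.

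The cost is analysis wording, plus one degree of freedom in each model for the added term. No new data are needed. Duration is recalled by participants, so it carries error and adjustment will be incomplete to that extent. Fixing this before the follow-up data are analysed also avoids a post hoc choice of covariate.
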